## 4 Design of the Study

---

### 4.1 Objectives of the Study

---

The primary objective of this study is to evaluate whether sodium-glutamate antagonist riluzole in a dose of 50mg BID 14 days prior to the surgery and 28 days following the surgery is superior to placebo in achieving better neurological outcomes in patients undergoing surgical decompression for moderate or severe cervical spondylotic myelopathy.

Secondary objectives are to evaluate differences between the investigational and the control group as measured by pain, functional and quality of life outcomes, health utilities, and adverse events.

#### 4.1.1 Primary Endpoint

---

- Absolute change in mJOA from admission to 180 days

#### 4.1.2 Secondary Efficacy Endpoints

---

- Absolute change in Nurick score from admission to 180 days
- Absolute change in SF-36v2.0™ PCS from admission to 180 days
- Absolute change in Neck Disability Index (NDI) from admission to 180 days
- Absolute change in Cervical Pain Numeric Rating Scale from admission to 180 days
- Absolute change in EQ-5D utility score from admission to 180 days
- Absolute change in ASIA Motor score from admission to 180 days
- Absolute change in ASIA Sensory score from admission to 180 days
- Absolute change in Grip Strength from admission to 180 days
- Rate of neurological complications

#### 4.1.3 Other Endpoints

---

- Absolute change in mJOA score from admission to 35 days and 365 days
- Absolute change in Nurick score from admission to 35 days and 365 days
- Absolute change in SF-36v2.0™ PCS score from admission to 35 days and 365 days
- Absolute change in NDI score from admission to 35 days and 365 days
- Absolute change in SF-36v2.0™ MCS score from admission to 35 days and 365 days
- Absolute change in SF-36v2.0™ eight dimensions from admission to 35 days and 365 days
- Absolute change in EQ-5D from admission to 35 days and 365 days
- Absolute change in ASIA Motor Score from admission to 35 days and 365 days
- Absolute change in ASIA Sensory Score from admission to 35 days and 365 days
- Absolute change in Grip Strength from admission to 35 days and 365 days
- Absolute change in Cervical Pain NRS from admission to 35 days and 365 days
- Absolute change in Bazaz Dysphagia Score from admission to 35 days and 365 days
- Systemic (non-neurological) complications

## Efficacy of Riluzole in Patients with Cervical Spondylotic Myelopathy Undergoing Surgical Treatment. A Randomized, Double-Blind, Placebo-Controlled, Multi-Center Study

- Changes in all outcome parameters (mJOA, Nurick, SF36v2, NDI, EQ-5D, ASIA Motor Score, ASIA Sensory Score, Grip Strength, Cervical Pain NRS and, Bazaz Dysphagia Score) between -14 days and the pre-operative visit
- Changes in outcome parameters over follow-up time (-14, admission, 35, 180 and, 365 days).

### 4.1.4 Safety Evaluation

---

Incidence of adverse events (AE) will be summarized by body system and preferred term. All AEs will be listed and abnormal lab values reviewed. AEs will be adjudicated for relationship to the investigational drug.

### 4.2 Selection of Investigators

---

Investigators will be selected among the AOSpine North America Research Network associated research centers. All AOSpine North America Research Network investigators are registered orthopedic and neurological surgeons who meet the credentials at their institution for performing spine surgical procedures. The surgical procedures used in this study are considered standard of care. Selected investigational site will provide evidence of qualification for conducting clinical research to Sponsor /CRO.

### 4.3 Inclusion Criteria

---

- Signed informed consent
- Age between 18 and 80 years
- Diagnosis of symptomatic cervical spondylotic myelopathy defined as a combination of:
  - (1) one or more of the following symptoms:
    - Numb hands
    - Clumsy hands
    - Impairment of gait
    - Bilateral arm paresthesiae
    - l'Hermitte's phenomena
    - Weakness
  - And,
  - (2) one or more of the following signs:
    - Corticospinal distribution motor deficits
    - Atrophy of hand intrinsic muscles
    - Hyperreflexia
    - Positive Hoffman sign
    - Upgoing plantar responses
    - Lower limb spasticity
    - Broad based, unstable gait
  - And,
  - (3) MRI evidence of cervical spondylotic myelopathy
- Scheduled for an elective surgery for cervical spondylotic myelopathy
- mJOA score  $\geq 8$  and  $\leq 14$  at screening

Efficacy of Riluzole in Patients with Cervical Spondylotic Myelopathy Undergoing Surgical Treatment. A Randomized, Double-Blind, Placebo-Controlled, Multi-Center Study

- Women must be:
  - Postmenopausal defined as amenorrhea for at least 2 years.
  - Surgically sterile, (have had a hysterectomy or bilateral oophorectomy, tubal ligation, or otherwise be incapable of pregnancy)
  - Abstinent (at the discretion of the investigator)
  - Having other congenital or medical condition that prevents subject from becoming pregnant
  - If sexually active, be practicing an effective method of birth control such as hormonal prescription oral contraceptives, progesterone implants or injections, intrauterine device (IUD), or male partner with a vasectomy. A double-barrier method such as condoms, diaphragms or cervical caps with spermicidal foam, cream or gel may be used as a birth control method.
  - Women of childbearing potential must have a negative serum  $\beta$ -human chorionic gonadotropin ( $\beta$ -hCG) pregnancy test or a negative urine pregnancy test at screening before the first dose of study drug is received.

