|                                                            | 
And,
 
(3) MRI evidence of cervical spondylotic myelopathy
 
 
• Scheduled for an elective surgery for cervical spondylotic myelopathy
 
• mJOA score <math>\geq 8</math> and <math>\leq 14</math> at screening
 
• Women must be: 
 
○ Postmenopausal defined as amenorrhea for at least 2 years.
 
○ Surgically sterile, (have had a hysterectomy or bilateral oophorectomy, tubal ligation, or otherwise be incapable of pregnancy)
 
○ Abstinent (at the discretion of the investigator)
 
○ Having other congenital or medical condition that prevents subject from becoming pregnant
 
○ If sexually active, be practicing an effective method of birth control such as hormonal prescription oral contraceptives, progesterone implants or injections, intrauterine device (IUD), or male partner with a vasectomy. A double-barrier method such as condoms, diaphragms or cervical caps with spermicidal foam, cream or gel may be used as a birth control method.
 
○ Women of childbearing potential must have a negative serum <math>\beta</math>-human chorionic gonadotropin (<math>\beta</math>-hCG) pregnancy test or a negative urine pregnancy test at screening before the first dose of study drug is received.
 
 
 
 |

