|                              | 
 
• Methoxsalen
 
• Mexiletine
 
• Oral contraceptives
 
• Phenylpropanolamine
 
• Thiabendazole
 
• Zileuton
 
 
Inducers:
 
 
• Montelukast
 
• Phenytoin
 
 
*Note: no washout period required; if these medications are discontinued, subjects are eligible to be enrolled in the trial.
 
 
• Systemic infection such as AIDS, HIV, and active hepatitis
 
• Active malignancy defined as history of invasive malignancy, except if the patient has received treatment and displayed no clinical signs and symptoms for at least five years
 
• Recent history (less than 3 years) of chemical substance dependency or significant psychosocial disturbance that may impact the outcome or study participation
 
• Breastfeeding at screening visit and plan to continue during the course of the study drug
 
• Unlikely to comply with the follow-up evaluation schedule
 
• Unlikely to comply with investigational drug regime
 
• Participation in a clinical trial of another investigational drug or device within the past 30 days
 
• Is a prisoner
 
• Unable to converse, read or write English at elementary school level
 
 |

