#### 4.4 Exclusion Criteria

---

- Previous surgery for CSM
- Concomitant symptomatic lumbar stenosis
- CSM symptoms due to cervical trauma (at the discretion of the investigator)
- Hypersensitivity to riluzole or any of its components
- Neutropenia measured as absolute neutrophil count (ANC) measured in cells per microliter of blood of  $< 1500$  at screening visit
- Creatinine level of  $> 1.2$  milligrams (mg) per deciliter (dl) in males or  $> 1.1$  milligrams per deciliter in females at screening visit
- Liver enzymes (ALT or AST) 3x higher than normal values at screening visit.
- Subject will be using any of the following medications which are classified as CYP1A2 inhibitors or inducers\* during the course of the drug regimen:

Inhibitors:

- Ciprofloxacin
- Enoxacin
- Fluvoxamine
- Methoxsalen
- Mexiletine
- Oral contraceptives
- Phenylpropanolamine
- Thiabendazole
- Zileuton

Inducers:

- Montelukast
- Phenytoin

\*Note: no washout period required; if these medications are discontinued, subjects are eligible to be enrolled in the trial

- Systemic infection such as AIDS, HIV, and active hepatitis

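### Oral contraceptives are accepted as birth control in section 4.3 but prohibited during dosing in section 4.4, and stopping them is not tied to a replacement method

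*Protocol*

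**What the plan says.** Protocol section 4.3 lists the conditions under which a woman may enter the trial. If she is sexually active she must "be practicing an effective method of birth control such as hormonal prescription oral contraceptives". The alternatives that follow are "progesterone implants or injections, intrauterine device (IUD), or male partner with a vasectomy", and a double-barrier method is also allowed. The synopsis has the same text: "If sexually active, be practicing an effective method of birth control such as hormonal prescription oral contraceptives".

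Protocol section 4.4 excludes a patient if the "Subject will be using any of the following medications which are classified as CYP1A2 inhibitors or inducers" "during the course of the drug regimen". The inhibitors listed there include "Oral contraceptives", without qualification by type. A footnote to the whole list reads "no washout period required; if these medications are discontinued, subjects are eligible to be enrolled in the trial". The synopsis carries the same list and note.

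Three other places bear on the point:

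- Section 3.2.1 states that riluzole is metabolized by CYP1A2, which is the reason for the exclusion.
- Section 4.5.2.3 (Visit 2, Enrollment) has the site verify all eligibility criteria, randomize, dispense the first bottle and advise the subject against drugs on the exclusion list, all at one visit. It does not mention changing contraceptive method.
- Table 1 schedules the pregnancy test at screening only.

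**The concern.** One of the stated ways to satisfy an inclusion criterion is itself an exclusion. A site can record the pill as the qualifying method at Visit 2 and must, at that same visit, tell the woman not to take it.

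The footnote sharpens the problem. For every other drug on the list, stopping removes the obstacle and has no bearing on any other criterion. For an oral contraceptive, stopping also removes the basis on which the woman may have met section 4.3. The footnote treats it like the rest.

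If a site does not make the connection, one of two things can follow. Either a prohibited inhibitor of riluzole metabolism continues into dosing, or contraception lapses around the first dose with no replacement expressly required. The protocol takes fetal exposure seriously: it requires contraception and a negative pregnancy test before dosing, and section 7.1.4 counts fetal distress, fetal death and birth defects as serious adverse events.

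**Working it through.** No power or sample-size figure is involved. The check sets the criteria side by side, works through the possible cases, and then computes the time available to switch.

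**How the two criteria are framed in time**

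- Inclusion (section 4.3): present tense, confirmed when eligibility is verified at Visit 2 (section 4.5.2.3).
- Exclusion (section 4.4): forward-looking, covering use during the regimen, which starts on the 14th day before surgery (section 4.5.2.3).

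**Cases for a sexually active woman of childbearing potential**

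1. *Uses a listed method other than the pill.* Meets the inclusion and does not trigger the exclusion. No problem.
2. *Stopped the pill before Visit 2.* Not excluded. She is no longer using the pill when eligibility is verified, so she must already have another effective method. No problem.
3. *On the pill at Visit 2 and will continue.* Meets the inclusion by its first example but is excluded by section 4.4. The two sections point in opposite directions, and the exclusion should govern.
4. *On the pill at Visit 2 and will stop before the first dose.* Meets the inclusion, because she is using a named method on the day of the check. Not excluded, because she will not use it during the regimen. The footnote supports enrollment on stopping. Nothing expressly requires another method by the first dose.

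Case 4 is the gap. The procedures for the admission, pre-discharge and 35-day visits (sections 4.5.2.4, 4.5.2.6 and 4.5.2.7) contain no contraception check and no repeat pregnancy test. Concomitant therapy is recorded at those visits, so continued pill use could come to light, but the earliest of them, admission, falls after the 14 days of preoperative dosing.

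**Time available to put a replacement in place**

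- Visit 2 window: 15 to 21 days before surgery (Table 1, sections 4.5.2.3 and 4.5.3).
- First dose: 14th day before surgery (section 4.5.2.3).
- Interval = Visit 2 day − 14, so 15 − 14 = 1 day to 21 − 14 = 7 days.
- Section 3.3 gives a different randomization window, 14 to 17 days before surgery. On that window the interval is 14 − 14 = 0 days to 17 − 14 = 3 days.

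**Period the replacement must cover**

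- Nominal dosing period = 14 days before surgery + 28 days after = 42 days (synopsis, section 3.3).

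**The case against.** The strongest reply is that the two lists can be read together. Eligibility means meeting every inclusion criterion and no exclusion, so an example in an inclusion criterion cannot override an exclusion. The methods in section 4.3 are illustrative, several others are named, and a woman can satisfy both sections by using one of them. Enrollment is randomization at Visit 2 (sections 4.5.3 and 4.6.2), so the footnote can be read as requiring the pill to be stopped already by then, which forces another method at the eligibility check. The contraception requirement also has no visit attached, whereas the mJOA score, pregnancy test and laboratory limits are tied to screening. It can therefore be read as a continuing duty. Finally, contraception advice may appear in the consent form or the drug insert.

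Much of this stands. The joint reading is reasonable, it disposes of cases 1 to 3, and a careful site will reach it. But the protocol does not state it, and up to 16 sites (section 3.3) would each have to infer it. The exclusion itself looks forward, so it leaves case 4 open. The footnote does not distinguish contraceptives from drugs whose withdrawal has no other consequence. The consent pages and drug insert are not available here, so what women are told in practice cannot be judged. The point concerns the wording of the criteria only, and whatever those materials say, the protocol still names a prohibited drug as an accepted method.

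**Conclusion.** The point holds. Sections 4.3 and 4.4, and the matching synopsis text, are inconsistent on oral contraceptives, and the footnote leaves one route by which a woman can meet the wording and begin dosing without contraception.

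The size is minor. The gap is confined to sexually active women of childbearing potential who are taking the pill at Visit 2, and the protocol gives no basis for estimating how many there will be. It has no effect on the primary endpoint, type I error, power or analysis populations. The mismatch between the two lists is plain on the page. The residual gap rests on reading the contraception requirement as confirmed at Visit 2 and the exclusion as applying from the first dose. It should be corrected because it touches subject safety and control of co-medication and costs little to put right, but it need not hold up the trial.

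**What to change.** Make two wording changes, each in the body and in the synopsis:

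1. In section 4.3 and the synopsis inclusion criteria, delete hormonal oral contraceptives from the accepted methods. Progesterone implants or injections, IUD, partner vasectomy and double barrier stay.
2. Add to the footnote in section 4.4 and in the synopsis exclusion criteria: *A woman who stops an oral contraceptive must have another listed effective method in place before the first dose and through the dosing period.*

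The no-washout rule is unchanged. The cost is four text edits and a notice to sites, with no added visits or tests.

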#### 4.4 Exclusion Criteria

---

- Previous surgery for CSM
- Concomitant symptomatic lumbar stenosis
- CSM symptoms due to cervical trauma (at the discretion of the investigator)
- Hypersensitivity to riluzole or any of its components
- Neutropenia measured as absolute neutrophil count (ANC) measured in cells per microliter of blood of  $< 1500$  at screening visit
- Creatinine level of  $> 1.2$  milligrams (mg) per deciliter (dl) in males or  $> 1.1$  milligrams per deciliter in females at screening visit
- Liver enzymes (ALT or AST) 3x higher than normal values at screening visit.
- Subject will be using any of the following medications which are classified as CYP1A2 inhibitors or inducers\* during the course of the drug regimen:

Inhibitors:

- Ciprofloxacin
- Enoxacin
- Fluvoxamine
- Methoxsalen
- Mexiletine
- Oral contraceptives
- Phenylpropanolamine
- Thiabendazole
- Zileuton

Inducers:

- Montelukast
- Phenytoin

\*Note: no washout period required; if these medications are discontinued, subjects are eligible to be enrolled in the trial

- Systemic infection such as AIDS, HIV, and active hepatitis

## Efficacy of Riluzole in Patients with Cervical Spondylotic Myelopathy Undergoing Surgical Treatment. A Randomized, Double-Blind, Placebo-Controlled, Multi-Center Study

- Active malignancy defined as history of invasive malignancy, except if the patient has received treatment and displayed no clinical signs and symptoms for at least five years
- Recent history (less than 3 years) of chemical substance dependency or significant psychosocial disturbance that may impact the outcome or study participation
- Breastfeed at screening visit and plan to continue during the course of the study drug
- Unlikely to comply with the follow-up evaluation schedule
- Unlikely to comply with investigational drug regime
- Participation in a clinical trial of another investigational drug or device within the past 30 days
- Is a prisoner
- Unable to converse, read or write English at elementary school level

### 4.5 Study Procedures

---

#### 4.5.1 Study Schematic

---

The schedule of visits and data to be collected at each visit is shown in Table 1. All visits must be performed in clinic. Data collection by phone and/or mail is not permitted.

Efficacy of Riluzole in Patients with Cervical Spondylotic Myelopathy Undergoing Surgical Treatment. A Randomized, Double-Blind, Placebo-Controlled, Multi-Center Study

**Table 1 Schedule of study activities**

|                                   | Screening | Enrollment
(15–21 days
before the
surgery) | Admission | Procedure
(Day 0) | Pre-
discharge | 35 days ± 5
days | 180 days ±
30 days | 365 days ±30
days | Unscheduled
Visit |
|-----------------------------------|-----------|-----------------------------------------------------|-----------|----------------------|-------------------|---------------------|-----------------------|----------------------|----------------------|
| Informed Consent                  | X         |                                                     |           |                      |                   |                     |                       |                      |                      |
| HIPAA
Authorization            | X         |                                                     |           |                      |                   |                     |                       |                      |                      |
| Inclusion/exclusion               | X         |                                                     |           |                      |                   |                     |                       |                      |                      |
| Pregnancy Test
(If applicable) | X         |                                                     |           |                      |                   |                     |                       |                      |                      |
| Demographics                      | X         |                                                     |           |                      |                   |                     |                       |                      |                      |
| Socio-economic                    |           | X                                                   |           |                      |                   |                     |                       |                      |                      |
| Health behavior                   |           | X                                                   | X         |                      |                   | X                   | X                     | X                    |                      |
| Medical History                   |           | X                                                   |           |                      |                   |                     |                       |                      |                      |
| Vitals                            |           | X                                                   | X         |                      | X                 | X                   |                       |                      |                      |
| Clinical lab                      | X         |                                                     | X         |                      |                   | X                   |                       |                      |                      |
| Myelopathy History                |           | X                                                   |           |                      |                   |                     |                       |                      |                      |
| Operative data                    |           |                                                     |           | X                    |                   |                     |                       |                      |                      |
| mJOA                              | X         | X††                                                 | X         |                      |                   | X                   | X                     | X                    |                      |
| Nurick score                      |           | X                                                   | X         |                      |                   | X                   | X                     | X                    |                      |
| NDI                               |           | X                                                   | X         |                      |                   | X                   | X                     | X                    |                      |
| Pain NRS                          |           | X                                                   | X         |                      |                   | X                   | X                     | X                    |                      |
| SF-36v2.0™                        |           | X                                                   | X         |                      |                   | X                   | X                     | X                    |                      |

Efficacy of Riluzole in Patients with Cervical Spondylotic Myelopathy Undergoing Surgical Treatment. A Randomized, Double-Blind, Placebo-Controlled, Multi-Center Study

|                                | Screening | Enrollment
(15–21 days
before the
surgery) | Admission | Procedure
(Day 0) | Pre-
discharge | 35 days ± 5
days | 180 days ±
30 days | 365 days ±30
days | Unscheduled
Visit |
|--------------------------------|-----------|-----------------------------------------------------|-----------|----------------------|-------------------|---------------------|-----------------------|----------------------|----------------------|
| EQ-5D                          |           | X                                                   | X         |                      |                   | X                   | X                     | X                    |                      |
| ASIA (Complete)                |           | X                                                   | X         |                      |                   | X                   | X                     | X                    |                      |
| Grip Strength                  |           | X                                                   | X         |                      |                   | X                   | X                     | X                    |                      |
| Bazaz Scale                    |           | X                                                   | X         |                      |                   | X                   | X                     | X                    |                      |
| Adverse Events                 |           |                                                     | X         | X                    | X                 | X                   | X                     | X                    | X                    |
| Concomitant
therapy         |           | X                                                   | X         |                      | X                 | X                   | X                     | X                    | X                    |
| Randomization                  |           | X                                                   |           |                      |                   |                     |                       |                      |                      |
| Study Medication
Dispensing |           | X                                                   | X         |                      |                   |                     |                       |                      |                      |
| Medication
Compliance Diary |           |                                                     | X         |                      |                   | X                   |                       |                      |                      |

†† mJOA needs to be repeated if older than 21 days or if patient's clinical manifestation has significantly worsened in investigator's opinion since the screening visit

